### Economic evaluation

A cost-effectiveness analysis will be performed to compare the health effects and costs of treatment according to the algorithm, as compared with current practice. Preventing major complications is likely to be cost saving, for example, by preventing admission to the ICU and decreasing the length of hospital stay. However, additional costs may also be introduced by increasing the need for diagnostic resources (e.g. biochemical tests and CT scans) and possibly also minimally invasive interventions. Therefore, it is important to assess whether these costs will be counterbalanced by future health effects and cost savings.

For calculation of cost-effectiveness from a healthcare perspective, the volume of healthcare consumption will be measured during the trial using an adapted version of the Medical Consumption Questionnaire (iMCQ). This questionnaire will measure healthcare utilization for medical expenses both in hospital and out of hospital, including but not limited to medication, invasive interventions, days in the hospital, outpatient visits after discharge and visits to the general practitioner. Unit costs will be derived from tariffs as described in the “Zorginstituut Nederland Kostenhandleiding” [35]. Medication costs will be derived from the “Zorginstituut Nederland Medicijnkosten” and, if dosages are missing in the iMCQ, standard dosages will be derived from the “Zorginstituut Nederland Farmacotherapeutisch Kompas”. For calculation of cost-effectiveness from a societal perspective, the Productivity Consumption Questionnaire (iPCQ) will be used to derive losses in productivity. Travel costs per individual will be calculated using average travel distances and standard tariffs from the Zorginstituut Nederland Kostenhandleiding in combination with the number of visits in the iMCQ. Health-related quality of life will be measured using the Euroqol 5 dimensions-5 levels questionnaire (EQ5D-5 L) at baseline and 90 days after pancreatic resection (i.e. end of follow up) [36]. Relevant outcomes will be extracted from case record forms and electronic health records at the end of follow up. The quality-of-life scores related to these outcomes will be derived from scientific literature for calculation of cost-effectiveness. Quality-adjusted life years (QALYs) will be calculated by multiplying the duration of time spent in a health state by the corresponding quality-of-life score, hence combining life years and quality of life.

Trial-based cost-effectiveness analysis (CEA) will be performed using the empirical data comparing current practice to best practice up to 90 days after the index pancreatic resection [37]. Missing data on either health effects or costs will be imputed using multiple imputation. An additional model-based CEA will be performed to extrapolate the trial results beyond the trial duration [38–40], because the short-term effects from implementation of the algorithm - if present - are likely to affect long-term outcomes as well. Besides having influence on the primary outcome, implementation of best practice might also influence the risk of pancreatic insufficiency and possibly survival, as patients are in a better clinical condition to receive adjuvant chemotherapy. Using mathematical modeling, short-term evidence from the PORSCH trial will be translated to more generic outcomes, such as survival and health status. Finally, using the mathematical model and additional evidence from the literature, a cost-effectiveness analysis will be performed calculating the long-term additional costs and QALYs when implementing the algorithm for a lifetime horizon.

The incremental cost effectiveness ratio (ICER) will be calculated for both the trial-based and model-based CEA by dividing the difference in costs between usual care and the intervention by the difference in QALYs between usual care and the intervention. Sensitivity analysis will be performed on parameters that are expected to have the largest uncertainty. Bootstrapping and probabilistic sensitivity analysis will be performed in the trial-based and model-based CEA, respectively, to determine the uncertainty surrounding incremental health effects and costs. Results from these uncertainty analyses will be used to create (incremental) cost-effectiveness planes to graphically represent these results [40]. Cost-effectiveness acceptability curves will be calculated to demonstrate the probability that the intervention strategy will be cost-effective compared to current practice when using a range of cost-effectiveness thresholds (i.e. the amount society is willing to pay for an additional QALY).

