### Participants

Pancreatic surgery is centralized in The Netherlands in centers performing at least 20 pancreatoduodenectomies annually. All centers performing pancreatic surgery in The Netherlands are participating in this trial. All patients undergoing all types of pancreatic resection in these centers are identified and will be recruited in this trial. There are no exclusion criteria for centers or patients (i.e. nationwide complete enumeration).

Data will be extracted from the prospective Dutch Pancreatic Cancer Audit. Additional data on clinical outcomes will be extracted prospectively through continuous systematic evaluation of patient charts using a predefined case record form. Data are stored on a central secured data capturing tool (i.e. Castor EDC) containing programmed checks for outliers. To ensure patient confidentiality, the data stored centrally will be cleaned to remove all information that could directly trace back to an individual patient, and a unique patient identifier number will be assigned to every patient. The local principal investigator will have access to the identifiable patient information. The data entered will be checked by a senior researcher. Local principal investigators are responsible for data collection. They can delegate this to the study personnel if resources are not available at the center.

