**Fig. 6 Fig6:**
[figure not shown]
Removal of abdominal drains. Schematic overview of the removal of abdominal drain(s). ml, milliliter

To facilitate clinical use of this complex algorithm, it was incorporated in a smartphone application that should be filled out daily for every patient. Access to this application was granted to all clinicians participating in the trial. The application will provide multilevel advice based on the clinical and biochemical parameters entered daily. The application will not contain information that can be traced back to an individual patient. All data will be stored on a secure central database that is accessible to the study coordinators 24 h a day, 7 days a week. This was used to evaluate adherence to the study protocol. Local caregivers are contacted and reminded of the application when it is not filled out for every patient in the early afternoon, so that CT and potential drainage (if indicated) can still be performed on the same day.

Since clinical decision-making on invasive intervention in these patients is challenging, an expert panel is available to assess the indication for and feasibility of percutaneous drainage in the management of pancreatic fistula. This online panel, consisting of dedicated radiologists with expertise in abdominal radiology, interventional radiologists and surgeons with expertise in pancreatic surgery, is available 24 h a day, 7 days a week. The advice will be reported back to the clinician within 12 h after consultation or when at least three experts provide their advice on the next step in the management of these patients. The organization of this expert panel will be similar to the Dutch Pancreatitis Study Group expert panel [17].

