The management of pancreatic fistula after pancreatic resection is shifting from relaparotomy to a more conservative approach using minimally invasive catheter drainage. Pancreatic fistula after pancreatoduodenectomy leads to an intra-abdominal fluid collection filled with activated pancreatic juices. When drained adequately, even a severe pancreatic fistula could resolve with primary catheter drainage alone [9]. In addition, percutaneous drainage is a minimally invasive procedure, which will provoke less surgical trauma (i.e. tissue injury and systemic inflammatory response) compared with relaparotomy. Even moderately small surgical trauma that induces a proinflammatory cytokine response can lead to organ failure in severely ill patients [12]. There is, however, still a significant number of patients in whom pancreatic fistula is managed primarily through laparotomy. Clinical outcomes might be improved using a step-up approach with primary catheter drainage and relaparotomy as a salvage option in patients who continue to deteriorate without further options for minimally invasive drainage.

This trial has several limitations. Even though a stepped-wedge, cluster-randomized trial is less efficient as compared with a conventional individual randomized trial, this is the only appropriate design to evaluate our research question, which is based on education in “best practice care” involving early detection and management of pancreatic fistula. With a design based on individual-level randomization, contamination of the control group would have been very likely due to the learning effect of applying the algorithm in the intervention group. The more efficient, cluster-randomized, cross-over design, in which half of the clusters crosses over from control to intervention and the other from intervention to control, is also prohibited due to the learning effect. Moreover, a stepped-wedge design was also chosen for logistical reasons, i.e. the aim is to implement the algorithm in all Dutch pancreatic centers and it is not feasible to roll out an education-based intervention with very active participation of the study team in more than one center simultaneously. Additionally, after calculating the statistical efficiency, the power achieved from a stepped-wedge, cluster-randomized trial was considerably higher than that of a parallel cluster-randomized trial, which is due to relatively high intra-cluster correlation.

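### In-hospital resource use is costed from a questionnaire and missing costs are imputed with no rule for patients who die, although charts already record the main hospital items

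*Protocol article*

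**What the plan says.** The Economic evaluation section of the protocol article makes the iMCQ the source of volumes for the healthcare perspective: "the volume of healthcare consumption will be measured during the trial using an adapted version of the Medical Consumption Questionnaire (iMCQ". Its scope includes the admission itself: "This questionnaire will measure healthcare utilization for medical expenses both in hospital and out of hospital". The items are described as "including but not limited to medication, invasive interventions, days in the hospital, outpatient visits after discharge and visits to the general practitioner". On gaps in the data, the section says: "Missing data on either health effects or costs will be imputed using multiple imputation". It gives no separate rule for the costs of patients who die.

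Charts appear once in that section: "Relevant outcomes will be extracted from case record forms and electronic health records at the end of follow up". The next sentence attaches literature quality-of-life scores to those outcomes, so as written they serve the effect side and not the cost side.

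Elsewhere, the Participants section describes chart review for the trial population, which has no exclusion criteria: "Additional data on clinical outcomes will be extracted prospectively through continuous systematic evaluation of patient charts using a predefined case record form". The Outcomes section lists CT scans, invasive (re-)interventions, ICU admission and stay, hospital stay and readmission among the secondary endpoints.

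**The concern.** The section expects savings mainly from fewer ICU admissions and shorter hospital stays. As written, it measures use in hospital with a questionnaire, although ICU stay, hospital stay and interventions are also trial endpoints collected from charts.

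A questionnaire that a patient must complete is lost when the patient dies or is too ill to answer. Death is a component of the primary endpoint, and the algorithm is meant to reduce it. Loss of cost data would then depend on outcome and, through the outcome, on study phase. If no patient who died has an observed cost, a death term in the imputation model cannot be estimated from the data, and the model can only extrapolate from survivors. Costs after the date of death are true zeros and not missing values, but nothing in the text prevents them from being imputed.

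At stake are the trial-based cost difference, the incremental cost-effectiveness ratio built on it, and the lifetime model as far as it uses the trial's costs. The clinical primary analysis is not affected.

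**Working it through.** The plan states no cost figure, so there is nothing to reproduce. The check has two parts.

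**1. Sources side by side**

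| Item | Source named for costing (Economic evaluation) | Also collected (Participants, Outcomes) |
|---|---|---|
| Hospital days | iMCQ | Yes, length of stay and readmission |
| Invasive interventions | iMCQ | Yes, number, timing and type |
| ICU stay, CT scans | Not itemised; iMCQ is the stated volume source and its list is open | Yes |
| Outpatient and general practitioner visits | iMCQ | Not listed |
| Patients who die | Multiple imputation, no separate rule | Chart review covers all patients |

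The questionnaire is needed for the fourth row. For the hospital rows, the trial already holds a source that does not depend on the patient being able to respond.

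**2. Scale if decedents' costs are replaced by survivors' costs**

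Let m0 and m1 be mortality before and after implementation, and r the ratio of mean decedent cost to mean survivor cost. Set mean survivor cost to 1 and assume that it is the same in both phases.

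- True mean cost in a phase: (1 − m) + m·r = 1 + m(r − 1).
- True saving from fewer deaths: (m0 − m1)(r − 1).
- Saving seen if every decedent is given the survivor mean: 1 − 1 = 0.
- Difference missed: (m0 − m1)(r − 1).

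Inputs: the Background section gives an interquartile range across centers of 0–8% for in-hospital mortality after pancreatoduodenectomy. That corresponds to 0 to 0.08 × 1186 = 95 deaths in the required sample, or 0 to 0.08 × 1600 = 128 among all resections. Halving mortality (m1 = m0/2) is an assumption that borrows the 50% relative reduction planned for the composite endpoint. All values of r are assumptions.

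| m0 | m1 | r | (m0 − m1)(r − 1), share of mean survivor cost |
|---|---|---|---|
| 2% | 1% | 1.5 | 0.01 × 0.5 = 0.5% |
| 4% | 2% | 2 | 0.02 × 1 = 2% |
| 8% | 4% | 3 | 0.04 × 2 = 8% |
| 4% | 2% | 1 | 0.02 × 0 = 0 |
| 4% | 2% | 0.5 | 0.02 × (−0.5) = −1% |

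These figures are worst cases for each set of inputs: all decedent costs are missing, and the imputation uses nothing that distinguishes decedents. If a share q of decedents lacks costs in both phases, each figure is multiplied by q. An error of a few percent of the mean can still matter, because the incremental cost is itself a difference between two phase means.

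**The case against.** Three replies have force.

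- The article calls the iMCQ adapted and names no respondent. A proxy or staff member might complete it, and then deaths need not leave a gap. This stands as a limit: completion by the patient is likely but inferred.
- Nothing forbids chart data for costing. That is true, but the section names a source for volumes, extends it to hospital care, and links the records only to outcomes and quality-of-life scores. It is a stated choice and not an omission.
- The imputation model is analysis-plan content and could include death, ICU days and length of stay. Chart volumes as predictors would reduce the problem. However, volumes that are available as predictors can be costed directly, which is simpler and needs no model.

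The planned bootstrapping and sensitivity analyses describe uncertainty and would not by themselves correct a biased source.

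A reader might also infer that the cost of delivering the algorithm is left out. The Intervention section says "Local caregivers are contacted and reminded of the application when it is not filled out for every patient in the early afternoon", and the Discussion says "it is not feasible to roll out an education-based intervention with very active participation of the study team in more than one center simultaneously", yet the economic section mentions neither reminders nor training nor the expert panel. The documents do not support that reading. The article condenses a fuller protocol, does not exclude such costs, keeps an open item list, and acknowledges extra tests, CT scans and interventions. Itemised delivery costing is commonly left to a fuller plan.

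**Conclusion.** The point holds as a risk of bias in a secondary analysis. In-hospital volumes are assigned to a questionnaire, missing costs are imputed, and deaths have no rule, while chart data on the main hospital cost drivers are already collected. Under the stated assumptions the missed cost difference runs from 0.5% to 8% of mean survivor cost, with 2% at 4% mortality and a cost ratio of 2.

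A reader might go further and conclude that the cost-effectiveness result will be wrong, or that savings will be understated. The documents do not show this. The error vanishes if decedents cost the same as survivors and reverses if they cost less, which is possible because early death ends cost accrual. The conclusion also rests on patients completing the questionnaire, which is not stated. The change is worth making because cost-effectiveness is a stated aim and the better source is already at hand.

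**What to change.** State the following in the economic analysis plan:

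1. In-hospital volumes (hospital and ICU days, CT scans, drainage, reoperation, readmission) come from the case record form and hospital records for every patient, decedents included.
2. The iMCQ is used for out-of-hospital care only.
3. Costs after the date of death are set to zero and are never imputed.
4. Missing out-of-hospital costs are imputed only for time alive after discharge, with death and chart-recorded resource use in the imputation model. This includes patients discharged alive who die before day 90. Limiting imputation to survivors would drop real costs of these patients.

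Some extrapolation remains under item 4, but it is confined to out-of-hospital care. The cost is extra analysis work to link chart data to unit costs. The hospital items listed are already within the trial's data collection.

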Secondary endpoints include individual components of the composite endpoint and an adapted version of the primary endpoint in which only complications are included that are deemed by the blinded adjudication committee to be directly related to a pancreatic fistula. Other secondary endpoints are: the Comprehensive Complication Index (CCI) [25] based on complications grade 3 or higher according to the Clavien-Dindo classification [19], postoperative pancreatic fistula [21], gastroenterostomy leakage, postoperative bile leakage [22], delayed gastric emptying [23], chyle leakage [26], new-onset acute pancreatitis [24], number and timing of abdominal CT scans, number, timing and type of invasive (re-)interventions, admission to the Intensive Care Unit (ICU), length of ICU stay, length of hospital stay, readmission rate, number of patients receiving adjuvant chemotherapy at 90 day follow up, duration of postoperative pancreatic fistula (time to removal of the last abdominal drain or completion of pancreatectomy), success of implementation (i.e. based on number and timing of abdominal CT scans and proportion of patients’ days in which the algorithm was not followed). Daily data on the incidence and duration of SIRS, sepsis and organ failure (according to the definitions in Table 1 and according to Sequential Organ Failure Assessment (SOFA) and the Multiple Organ Dysfunction Score (MODS)) are also collected [27–29]. In addition, we aim to evaluate the impact on quality of life, total direct and indirect costs and budget impact (see “Economic evaluation”).

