The primary endpoint (i.e. composite of post-pancreatectomy bleeding, new-onset organ failure and death) is a binary variable that will be analyzed using mixed-effects logistic regression analysis. Secondary endpoints will be analyzed using crude and adjusted mixed-effects logistic regression analysis (for binary outcomes) or mixed-effects linear regression analysis (for continuous outcomes). Crude analysis will include a random intercept and random slope at the level of the hospital to adjust for the design, and no other covariates. Adjusted analysis will additionally include the following covariates: calendar time and time since cross-over as a continuous variable, predictors for postoperative pancreatic fistula (i.e. soft pancreatic texture, small-diameter pancreatic duct, increasing blood loss during pancreatic resection and underlying disease that is *not* pancreatitis or pancreatic adenocarcinoma [33]) and predictors for the primary endpoint (i.e. male gender, increasing age, American Society of Anesthesiologists (ASA) classification > 2, index pancreatic resection pancreatoduodenectomy; based on multivariable logistic regression analysis as presented in Table 4). Relevant model assumptions (such as distribution of residuals) will be checked for all models; if deviations from the analysis plan are required this will be described. Crude and adjusted odds ratios with 95% confidence interval and *p* value will be reported.

**Table 4 Tab4:** Factors associated with the composite primary endpoint in 1686 patients undergoing pancreatic resection in the Dutch Pancreatic Cancer Audit

Outcome	Univariable		Multivariable	
	OR (95% CI)	*P* value	OR (95% CI)	*P* value
Male gender	1.64 (1.20–2.23)	0.002	1.64 (1.19–2.27)	0.002
Age	1.02 (1.01–1.04)	0.003	1.02 (1.00–1.03)	0.04
BMI	1.00 (1.00–1.01)	0.52		
ECOG performance score		0.17		
2 vs. 1	1.29 (0.92–1.79)	0.14		
3 vs. 1	1.59 (0.95–2.66)	0.08		
4 vs. 1	0.44 (0.06–3.33)	0.43		
ASA classification (3 and 4 vs. 1 and 2)	1.87 (1.33–2.61)	< 0.001	1.79 (1.26–2.53)	0.001
Preoperative additional nutrition		0.05		
Oral vs. none	0.98 (0.70–1.38)	0.91		
Via nasogastric tube vs. none	1.74 (0.92–3.28)	0.90		
Via TPN vs. none	4.04 (1.17–14.02)	0.03		
Preoperative biliary drainage	0.97 (0.71–1.32)	0.82		
Distal pancreatectomy vs. pancreatoduodenectomy	0.50 (0.31–0.79)	0.003	0.58 (0.36–0.94)	0.03
Texture pancreas (hard/firm vs. soft/normal)	1.22 (0.86–1.73)	0.26		

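### The only stated model for continuous outcomes omits baseline EQ-5D-5L, so the 90-day quality-of-life comparison is less precise than the collected data allow

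*Protocol article*

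**What the plan says.** Under Economic evaluation the article sets two measurement times: "Health-related quality of life will be measured using the Euroqol 5 dimensions-5 levels questionnaire (EQ5D-5 L) at baseline and 90 days after pancreatic resection". Quality of life is also an aim of the trial. The Background includes it among the outcomes on which superiority will be evaluated, and Outcomes, straight after the list of secondary endpoints, adds that "we aim to evaluate the impact on quality of life, total direct and indirect costs and budget impact", with a pointer to Economic evaluation.

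Statistical analysis assigns mixed-effects linear regression to continuous secondary endpoints, in two forms:

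- Without covariates: "Crude analysis will include a random intercept and random slope at the level of the hospital to adjust for the design, and no other covariates".
- With a named list, given in the next sentence of that section: "Adjusted analysis will additionally include the following covariates: calendar time and time since cross-over as a continuous variable, predictors for postoperative pancreatic fistula". The fistula predictors are pancreatic texture, duct diameter, blood loss and underlying disease. Predictors of the composite endpoint follow: sex, age, ASA class and type of resection.

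Economic evaluation gives no separate regression model for EQ-5D. It describes the cost-effectiveness ratio as obtained "by dividing the difference in costs between usual care and the intervention by the difference in QALYs between usual care and the intervention". For the cost-effectiveness calculation it takes the scores attached to recorded outcomes from the literature. It does not say whether, or how, the patients' own questionnaire values enter the QALY.

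**The concern.** A baseline measurement of the outcome is normally among the best predictors of its later value, and here it is already collected. The adjusted list was built for other outcomes: it brings duct diameter and gland texture into a quality-of-life model but leaves out the patient's own starting value. This is more than detail left to a fuller document, because the article goes down to named covariates and anyone following them would omit baseline EQ-5D.

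At stake is the width of the confidence interval for the 90-day EQ-5D difference. Patients are not individually randomized, and the two phases differ in calendar time and in the mix of centers. A chance difference in baseline health between the phases is therefore possible, and without the baseline value in the model it stays in the estimate.

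**Working it through.** **Inputs from the article (Sample size calculation):** 17 centers, one per sequence; 18 periods; 3.9 patients per center per step (Table 3, 17 centers); ICC 0.009; 13.8% reduced by half to 6.9%; two-sided alpha 0.05; power 0.80; required sample 1186.

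**Step 1: reproduce the plan's own figure, to confirm the layout.** The pooled two-proportion formula without continuity correction gives 305 per arm, 610 in total. With k = 17 steps and n patients per cell, the stepped-wedge design effect is

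[1 + ICC(kn + n − 1)] / [1 + ICC(kn/2 + n − 1)] × 3(1 − ICC) / [2(k − 1/k)].

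Solving for n gives 3.85. The first factor is 1.615/1.320 = 1.223, the second is 2.973/33.88 = 0.0877, and the design effect is 0.107. Then 610 × 0.107 ≈ 65.5 per period; 65.5/17 = 3.85 per cell; 3.85 × 17 × 18 ≈ 1178. The stated figure is 1186, a difference of 0.6%. The layout is confirmed, but this number concerns the primary endpoint and does not depend on the present point.

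**Step 2: effect of adjusting 90-day EQ-5D for baseline.** Assumptions not in the article:

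- a baseline-to-day-90 correlation ρ, shown as a range;
- the ICC of 0.009, estimated for the composite endpoint, also applies to EQ-5D;
- 4 responders per cell, which means near-complete questionnaires.

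Total variance is set to 1. The between-center variance is 0.009 and is left untouched. The within-center variance is 0.991 × (1 − ρ²). The variance of the intervention effect is obtained by generalized least squares with center as a random intercept and linear calendar time. Categorical time gives the same ratios.

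| ρ | 1 − ρ² | Variance ratio, adjusted / unadjusted | CI width, √ratio | Power for an effect with 80% power unadjusted |
|---|---|---|---|---|
| 0.3 | 0.91 | 0.92 | 0.96 | 83% |
| 0.4 | 0.84 | 0.86 | 0.93 | 86% |
| 0.5 | 0.75 | 0.78 | 0.88 | 89% |
| 0.6 | 0.64 | 0.68 | 0.83 | 92% |

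The last column is Φ((1.96 + 0.84)/√ratio − 1.96). The variance reduction is thus 1 − 0.92 = 8% at ρ = 0.3 and 1 − 0.68 = 32% at ρ = 0.6. It is slightly smaller than ρ² because the between-center part is not reduced.

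**Step 3: the QALY, conditional only.** If the trial-based QALY were the area under a straight line between a patient's two EQ-5D values, a baseline difference d between phases would add d × (90/365)/2 = 0.123d directly. That is 0.0012 QALY for each 0.01 of difference. The article states neither this construction nor any baseline difference.

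**The case against.** The strongest reply is that the covariate list was never meant for EQ-5D. Outcomes sets quality of life apart from the listed secondary endpoints and refers it to Economic evaluation, and Statistical analysis does not mention EQ-5D. It is fair that the link is not spelled out. But Economic evaluation offers no other model for comparing EQ-5D between phases, and the Background promises an evaluation of superiority, so the rule for continuous outcomes is the only one a reader can apply.

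A reader might go further and infer that the QALY difference, and with it the cost-effectiveness ratio, is biased by baseline differences and could even change sign. The documents do not support this, for four reasons:

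- The scores attached to recorded outcomes come from the literature for the cost-effectiveness calculation. If those alone form the QALY, baseline EQ-5D does not enter it and the carry-over is zero.
- The sentence on the ratio is a general definition that covers both the trial-based and the model-based analysis. A regression-adjusted difference would satisfy it equally well.
- Straight-line interpolation between the two questionnaires appears nowhere in the article.
- The order of cross-over is randomized. Where the adjusted model is used, its calendar-time and hospital terms leave mainly chance imbalance, which is imprecision rather than systematic bias. The planned bootstrapping already displays such uncertainty.

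It also stands that the size of the precision gain rests on a correlation the article does not give, and that no primary result is touched.

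**Conclusion.** The point holds for the 90-day EQ-5D comparison. The baseline value is collected, superiority in quality of life is to be evaluated, and the only stated model for continuous outcomes leaves the baseline out of both its forms. Some precision is lost at any non-zero correlation. For an assumed correlation of 0.3 to 0.6, adjustment would lower the variance of the effect by about 8% to 32%, which narrows the confidence interval by about 4% to 17%. It would also correct for chance baseline imbalance between phases. These figures assume that the ICC of 0.009 carries over to EQ-5D and that questionnaires are nearly complete.

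For QALYs the point is conditional on patients' own EQ-5D values being used, which the article leaves open. No conclusion about bias in the cost-effectiveness ratio follows. This is an inexpensive improvement to one non-primary comparison; the primary endpoint and the sample size of 1186 are unaffected.

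**What to change.** 1. In Statistical analysis, state that the adjusted mixed-effects linear model for 90-day EQ-5D-5L also includes baseline EQ-5D-5L utility, with missing baseline values imputed under the multiple imputation already planned for baseline data.
2. In Economic evaluation, state which scores form the trial-based QALY. Only if these are the patients' own EQ-5D values, estimate the incremental QALY as the study-phase coefficient from a regression that also contains baseline utility, calendar time and center, refitted in each bootstrap sample.

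The cost is a few sentences in the protocol or analysis plan. No new data, visits or staff are needed, and one more covariate in a linear model uses a negligible share of the degrees of freedom.
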